## ETHICS

Permission will be obtained from The Regional Committees on Health Research Ethics for Southern Denmark. The project is notified to the Regional Register of Health Related Research. Patients will follow the standard surveillance of cancer recurrence. Enrolled patients will not be exposed to further examinations with blood sampling or radiation, so there is no risk of physical harm for the patients. Patients randomised to the control-group will still be handled according to current standards and not receive any less attention.

No research indicates side effects of Internet-based treatment to cancer survivors. The assigned psychologist will register and follow any serious adverse effects until the problem is solved, stabilized or association with the study has been dismissed. Serious adverse effects will be reported to sponsor in one working day. Sponsor will report to the Ethical Committee once a year.

The participants can at all time withdraw from the study without explanation.

Participants are covered by "Patienterstatningen". No remuneration will be offered. The Helsinki declaration will be met.

The project may give new knowledge about improved care for cancer survivors and thus the benefits outweigh the potential harms.

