**Part 2 b, randomization**

*If randomized to augmented TAU:* The control group is described as “augmented” as the diagnostic telephone interview exceeds standard treatment. Furthermore, if randomized to augmented TAU the information letter (appendix 7. Informationsbrev) send to E-boks will include a reference to a website with a non-guided, publicly available E-learning program in cancer rehabilitation hosted by the Region of Central Jutland (livogkraeft.rm.dk). The website includes, besides a written material, self-help instructions for meditation. Use of the website will not be monitored.

*If randomized to TG-iConquerFear:* The information letter (Appendix 7. Informationsbrev) will contain a link to enter the platform directly. The assigned therapist will be informed simultaneously.

Both groups will follow standard surveillance according to national guidelines for cancer recurrence at a surgical or oncological department, which may include colonoscopy and/or CT scans. The municipality is responsible for rehabilitation and offers limited access to physical exercise, yoga, dieticians, psychologists, sexologists etc.

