### **Part 4, intervention**

The theoretical frame of iConquerFear[29] is based on the Common-Sense Model (CSM) of illness, the Self-Regulatory Executive Function model (S-REF; targets metacognitions) and Relational Frame Theory (RFT; theoretical basis for Acceptance and Commitment Therapy). The intervention includes elements of attention training, increasing metacognitive awareness, acceptance & mindfulness, promotion of expedient screening behaviour, and values-based goal setting. The platform is accessed through secure log-on and comprises 5 modules containing educational text, interactive exercises, short videos featuring doctors, therapists and patients' perspectives, see Fig. 3.

The Australian version of iConquerFear is completely self-directed.

The Danish version of iConquerFear will contain a messenger-function on the intervention dashboard, allowing the participant and therapist to communicate asynchronously (TG-iConquerFear). The participant is guided through the sessions by minimum weekly contact with an experienced therapist. The therapist will motivate, answer questions and give feedback on written material and exercises. The amount of contact will be recorded and explored as a moderator of intervention efficacy. Should any cancer-related questions occur, an oncologist or surgeon will be involved as a consultant to the therapists.

The programme can monitor adherence, dropouts and track log-ins and activity. A purpose-developed single-item questionnaire within the TG-iConquerFear will each week ask for level of engagement[47]. Participants who do not adhere to, or withdraw from, the intervention will be contacted by telephone and asked why. These participants will be asked if they would be willing to complete a post-intervention assessment and all follow-up assessments to aid intervention evaluation. Therapist assistance is scheduled to last 10 weeks, but the participants will have free access to the platform for another 6 months.

In case of recurrence during the 10 weeks of intervention, the participant will be excluded from analysis, but may continue in the programme.

Fig. 3, iConquerFear curriculum content

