## EVALUATION

### Primary outcome measure

The primary outcome measure is the 3 month follow-up (T1) total score on the recently validated Danish version of the FCRI [13]. The FCRI is a 42-item self-report measure that includes subscales assessing FCR triggers, severity, psychological distress, functioning impairments, insight, reassurance, and coping strategies [48]. The FCRI has demonstrated high: internal consistency ( $\alpha=0.96$ ) [49], interclass correlation (0.84) [13] and convergent validity in large heterogeneous cancer survivor samples. Respondents rate the degree to which symptoms/issues affected them over the past month on a Likert scale ranging from 0 ('not at all' or 'never') to 4 ('a great deal' or 'all the time'). While there are potential issues with aggregating FCRI subscales [50], total FCRI score will be used as the dependent variable, as it closely reflects proposed features of clinically significant FCR; namely related distress, functional impact, and maladaptive coping[2], rather than the level of fear indicated by the FCRI-SF [50, 51]. Total scores can range from 0-168; higher scores indicate greater FCR morbidity. Level of FCR will be measured post-treatment (T0) and at follow-up after 3 (T1) and 6 (T2) months. Long-term effect will be evaluated after one year (T3). All electronic questionnaires will be sent out automatically through RedCAP.

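### The plan has no arm-neutral route for ascertaining serious adverse effects: the only one named exists in the TG-iConquerFear arm alone

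*Combined protocol and SAP*

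**What the plan says.** The protocol's Ethics section sets the rule: "The assigned psychologist will register and follow any serious adverse effects". Follow-up of an event continues until it has resolved, has stabilised or is judged unrelated to the study. The next step is "Serious adverse effects will be reported to sponsor in one working day", and the sponsor then reports yearly to the ethics committee. No other person or channel is named.

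Under Part 2 b, randomization, a therapist appears only in the paragraph on TG-iConquerFear: "The assigned therapist will be informed simultaneously". Part 4, intervention, adds: "The participant is guided through the sessions by minimum weekly contact with an experienced therapist". It limits this support in time: "Therapist assistance is scheduled to last 10 weeks".

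For controls, Part 2 b describes a letter containing "a reference to a website with a non-guided, publicly available E-learning program in cancer rehabilitation", and adds: "Use of the website will not be monitored".

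Both arms then receive follow-up forms. Under Primary outcome measure: "All electronic questionnaires will be sent out automatically through RedCAP".

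The SAP (sections 3 to 5) lists no safety outcome, safety population or summary of harms.

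**The concern.** The protocol undertakes to register serious adverse effects and gives the task to someone whom only one arm has. Followed as written, one arm is observed at least weekly for a time and the other has no planned observer. A count of registered events by arm would then mix any real difference with a difference in how closely participants were watched. It could make the intervention look harmful because it was observed, or leave serious events among controls unnoticed. All participants entered at or above the FCRI cut-off of 22, so harms in untreated controls are a reasonable thing to want to know about. The Ethics section also says that controls will receive no less attention, which does not hold for the registration of serious events.

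**Working it through.** There is no stated figure to reproduce. The check is to trace every contact and data source after randomisation, by arm, and ask whether it is a planned route for recording serious adverse effects.

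| Source | TG-iConquerFear | Augmented TAU |
|---|---|---|
| Assigned person (Part 2 b; Ethics) | Yes | None named |
| Scheduled personal contact (Part 4) | At least weekly, 10 weeks | None described |
| Call on non-adherence or withdrawal from the intervention (Part 4) | Yes | Not described |
| Automatic follow-up forms (Fig. 2; Evaluation) | Yes, no adverse-event item listed | Yes, no adverse-event item listed |
| Registry hospitalisation and psychiatric drugs (Economic measures) | Planned, economic purpose | Planned, economic purpose |

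**Step 1: who the assigned psychologist is.** Ethics speaks of a psychologist and Part 2 b of a therapist. That they are the same person is an inference, but the only reading the text supports, because nobody is assigned to controls. Controls do speak to the primary investigator or a psychologist, but only for the telephone information and mini-SCAN interview, before consent and randomisation (Part 2, recruitment).

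**Step 2: how long the route lasts.** Scheduled support is 10 weeks. Follow-up is described as one year, while the intervals under Process of participation sum to 12 + 12 + 12 + 24 = 60 weeks.

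- Against 52 weeks: 10 / 52 = 19%.
- Against 60 weeks: 10 / 60 = 17%.

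Even in the intervention arm, scheduled therapist contact covers less than a fifth of follow-up.

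**Step 3: whether the forms fill the gap.** The follow-up instruments listed in Fig. 2 are the full FCRI, SCLs, BDS, Whiteley-8, QoL, MUIS, MCQ-30 and perceived risk. None is a report of serious events. The symptom scales can show worsening in both arms, but no section designates them as safety data.

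**Step 4: whether the registries fill the gap.** Hospitalisation with diagnosis would cover both arms. The stated purpose is cost-effectiveness and health care use, extraction comes at the end of the study, and the SAP update of 10 January 2025 says the registry-based economic analyses were not undertaken.

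**Result.** Planned routes for serious adverse effects after randomisation: one in the intervention arm, limited in time, and none in the control arm. Comparisons of harms planned in the SAP: none.

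**The case against.** Four arguments on the other side have weight.

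- **Silence is not a statement that events are lost.** A reader might infer that control-arm harms go unrecorded. The documents say only who registers events. Ad hoc reports from controls remain possible, and the questionnaires and participant letters are in appendices not available for this review. Fig. 2 may not be complete: it marks recurrence only at screening, yet recurrence at any follow-up is an exclusion criterion, which requires later information. This stands, so the point is limited to the absence of a planned route.
- **Worsening is measured.** A reader might infer that deterioration among controls is invisible, or that the arms cannot be compared on harm at all. That goes too far. Both arms complete the FCRI, SCL, BDS and Whiteley-8, and SAP section 5.3 already plans reliable change indices. What is missing is their designation as safety data and a commitment to report worsening by arm.
- **No comparison of harms is planned.** The SAP contains none, and Ethics describes case-by-case reporting of effects that may be linked to the study. A misleading comparison would therefore arise only if someone made one. This stands, and it limits the consequence to what may be claimed when harms are reported.
- **It may be too late.** The January 2025 update describes omitted analyses in the past tense, so new data collection may no longer be possible. This affects the remedy but not the finding.

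**Conclusion.** The point holds in this form: the protocol names no arm-neutral way to ascertain serious adverse effects, and its only named route exists in one arm, for a scheduled 10 weeks of about one year. Serious adverse effects registered this way cannot support a fair comparison between arms.

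The size of the imbalance in recorded events cannot be calculated. It would need a true event risk and a capture rate in each arm, and the documents give neither.

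The conclusion rests on two assumptions: that the assigned psychologist is the assigned therapist, and that the unseen appendices add no adverse-event item or contact route for controls. Neither the primary efficacy analysis nor any other analysis listed in the SAP is affected. The change is advisable because, without it, no credible comparative statement on serious harms can be made.

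**What to change.** **If follow-up is still open:** put one identical serious-adverse-event question in the T0–T3 REDCap forms for both arms. Have the answers logged by a study team member who is not treating that participant, for example the primary investigator. Naming the research assistant would not be enough, because Part 2, recruitment, defines that role as the primary investigator or one of the two psychologists who deliver the intervention. Report events by arm from this common source and list therapist-registered events separately. Spaced questionnaires cannot by themselves meet the one-working-day reporting rule, so returned answers must be actively checked.

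**In any case:**

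- Report by arm the number with reliable deterioration on the FCRI and SCL, using the reliable change indices of SAP section 5.3. This needs no new data.
- State the unequal ascertainment as a limitation.
- Make no comparative safety claim from therapist-registered events.

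**Cost:** a short amendment, one extra item at four time points and some staff time to follow up answers. More events will be reported overall. If follow-up has closed, the cost is one additional table and a paragraph of text.

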## RESEARCH PLAN

The protocol is part of a PhD project at the University of Southern Denmark planned from January 1st 2020 and the following 5 years parallel with specialist training, see Fig. 4 for elaboration.

Key dates:

May 2020: Extract data from RKKP

September 2020: Launch survey

October 2020: Inclusion of first participant

April 2022: RCT finish

May 2023: Final 1-year follow-up

January 2024: Extraction of retrospective economic data

Fig. 4, research and study plan

| Research and study plan                                                              |      |    |      |    |    |    |      |    |    |    |      |    |    |    |      |    |    |    |      |    |    |    |      |    |    |  |  |
|--------------------------------------------------------------------------------------|------|----|------|----|----|----|------|----|----|----|------|----|----|----|------|----|----|----|------|----|----|----|------|----|----|--|--|
|                                                                                      | 2018 |    | 2019 |    |    |    | 2020 |    |    |    | 2021 |    |    |    | 2022 |    |    |    | 2023 |    |    |    | 2024 |    |    |  |  |
| Activity                                                                             | Q4   | Q1 | Q2   | Q3 | Q4 | Q1 | Q2   | Q3 | Q4 | Q1 | Q2   | Q3 | Q4 | Q1 | Q2   | Q3 | Q4 | Q1 | Q2   | Q3 | Q4 | Q1 | Q2   | Q3 | Q4 |  |  |
| Preparation studies
- Protocol
- Ethics
- Review
- Fundraise
- REDCap |      |    |      |    |    |    |      |    |    |    |      |    |    |    |      |    |    |    |      |    |    |    |      |    |    |  |  |
| Specialist training                                                                  |      |    |      |    |    |    |      |    |    |    |      |    |    |    |      |    |    |    |      |    |    |    |      |    |    |  |  |
| Platform work
- Translate
- Test                                               |      |    |      |    |    |    |      |    |    |    |      |    |    |    |      |    |    |    |      |    |    |    |      |    |    |  |  |
| miniSCAN education & training                                                        |      |    |      |    |    |    |      |    |    |    |      |    |    |    |      |    |    |    |      |    |    |    |      |    |    |  |  |
| Launch survey (recruitment)                                                          |      |    |      |    |    |    |      |    |    |    |      |    |    |    |      |    |    |    |      |    |    |    |      |    |    |  |  |
| Perform miniSCAN (inclusion)                                                         |      |    |      |    |    |    |      |    |    |    |      |    |    |    |      |    |    |    |      |    |    |    |      |    |    |  |  |
| Platform work
- Pilot test                                                        |      |    |      |    |    |    |      |    |    |    |      |    |    |    |      |    |    |    |      |    |    |    |      |    |    |  |  |
| Launch RCT (intervention)                                                            |      |    |      |    |    |    |      |    |    |    |      |    |    |    |      |    |    |    |      |    |    |    |      |    |    |  |  |
| RCT runs                                                                             |      |    |      |    |    |    |      |    |    |    |      |    |    |    |      |    |    |    |      |    |    |    |      |    |    |  |  |
| Status / Evaluation                                                                  |      |    |      |    |    |    |      |    |    |    |      |    |    |    |      |    |    |    |      |    |    |    |      |    |    |  |  |
| Follow-up ½, 3, 6 & 12 months                                                        |      |    |      |    |    |    |      |    |    |    |      |    |    |    |      |    |    |    |      |    |    |    |      |    |    |  |  |
| Exchange in Australia                                                                |      |    |      |    |    |    |      |    |    |    |      |    |    |    |      |    |    |    |      |    |    |    |      |    |    |  |  |
| Analysing                                                                            |      |    |      |    |    |    |      |    |    |    |      |    |    |    |      |    |    |    |      |    |    |    |      |    |    |  |  |

Funding (VIP and TAP salary, statistical assistance, questionnaires, overhead e.g.) will be sought from public and private funds, and handled by the Department of Clinical Oncology, Vejle Hospital. The

Ph.D. student is a regular member of the Danish Cancer Society, but do not have any financial connection to any of the stakeholders.

## DISSEMINATION

Results will be published in international, peer-reviewed journals that reach an appropriate audience (open access where possible). The RCT will be registered at [www.clinicaltrials.gov](http://www.clinicaltrials.gov) with a reference to results. Data will be presented at national and international congresses. Negative, positive and inconclusive results will be published. An oral, public PhD defence will be held. If shown to be efficacious the results will be presented at cancer-treating departments throughout Denmark to encourage implementation. Results will be published at the Danish Cancer Society's webpage to inform future users. Study participants will if interested be mailed the results when the study is finished.

## Planned articles:

1. Therapist guided iConquerFear Protocol: Randomised controlled trial of therapist guided internet-delivered cognitive therapy for fear of cancer recurrence in colorectal cancer survivors vs. augmented treatment as usual
2. Fear of cancer recurrence in colorectal cancer survivors: A Danish population based study
3. Fear of cancer recurrence in colorectal cancer survivors screened to diagnosis
4. Fear of cancer recurrence in colorectal cancer survivors and association to functional disorders
5. Therapist guided iConquerFear targeting fear of cancer recurrence in colorectal cancer survivors

## DISCUSSION

This study is the first to analyse the effect of a therapeutic guided, Internet-based intervention for CRC survivors with clinical levels of FCR. The developmental process has included CRC survivors, oncology nurses, psychiatrists, psychologists, the Patient' and Relative's Council at Lillebaelt Hospital and doctors working in the field of oncology. Internet delivery was chosen, as many CRC survivors are working, and traditionally men are more reluctant to participate in face-to-face therapy. We believe this combination of a careful development and a considerate delivery will make TG-iConquerFear successful in reducing FCR and has the potential to target more men than face-to-face formats.

## PERSPECTIVES

This study will add to the current but sparse knowledge on optimal treatment of FCR among colorectal cancer survivors. Data from this project can be used directly as guidance in clinical daily life. At the current time no guidelines exists.

If successful, TG-iCF is proved effective in reducing psychological morbidity among colorectal cancer survivors and overall health care costs due to more appropriate use of health care services. Not only colorectal cancer survivors experiences fear of recurrence of disease, and TG-iCF have the

potential to be extended to multiple different diagnoses, including other cancer diagnoses but also survivors of cardiac arrest, acute lung embolism, TCI, apoplexies, etc.

## 1. Background and objectives

This SAP pertains to the randomized controlled trial evaluating the therapist-guided eHealth intervention TG-iConquerFear versus an augmented self-help control for reducing fear of cancer recurrence (FCR) in colorectal cancer survivors.

### Primary hypothesis

- TG-iConquerFear will result in a greater reduction in FCRI total score at 3 months post-intervention compared with control.

### Secondary hypotheses

- TG-iConquerFear will reduce anxiety, depression, and distress, and improve quality of life.
- TG-iConquerFear will not affect the prevalence of physical symptoms.
- Some participants will demonstrate particularly high engagement and adherence with the online format, which may be associated with distinct demographic or psychosocial characteristics.

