#### RCT

This study is a population based randomized controlled clinical superiority trial. Participants are randomized to internet-based, TG-iConquerFear or augmented TAU (1:1), see Fig. 1. All participants will follow the standard cancer follow-up program.

Fig. 1, Trial design

[figure not shown]

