### Secondary outcome measures

Change from baseline (Tb) to post-intervention (T0, T1, T2, T3) in the following outcomes

- *Bodily Distress Symptom/somatization, Anxiety and depression* evaluated by relevant Symptom Checklist-90-R (SCL) subscales [52], validated in Danish by Olsen et al [53].
- *Health Anxiety* measured by the validated [54] Whiteley-8 index [55].
- *Global quality of life and global health* measured by a VAS 0-100

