### Statistical analysis

A flowchart of participants and dropouts following the CONSORT guidelines will be drawn.

STATA will be used for all statistical analyses. All statistical tests will be two-sided (level of significance = 0.05).  $\chi^2$ -tests will be performed on all follow-up data to analyse proportions of participants above or below the clinical cut-off.

The influence of the intervention will be analysed for the primary outcome and for all secondary outcomes. Linear mixed effects models will be used to analyse longitudinal differences between intervention and control group. Association with functional disorders (health anxiety and bodily distress symptom) and psychiatric disorders (anxiety and depression) will be evaluated with adjusted and unadjusted linear regressions analyses on baseline data.

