### Secondary outcomes

- Anxiety, depression, and distress (validated scales).

- Health-related quality of life (EQ-5D-5L).
- Proportion of participants scoring above/below the FCRI-SF cut-off ( $\geq 22$ ).
- Adherence and engagement metrics (number of modules completed, communication with therapist).

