### 5.3 Secondary analyses

- Continuous secondary outcomes analyzed using paired *t*-tests and between-group comparisons of change scores.
- Longitudinal analyses across baseline, 1/2, 3, and 6 months using **linear mixed-effects models**, with fixed effects for group, time, and interaction, and random intercepts for subjects.
- Proportions above/below clinical cut-offs analyzed using  **$\chi^2$  tests**.
- Reliable and clinically significant change indices calculated.

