## 7. Multiplicity

- No formal adjustments planned. Secondary and exploratory analyses considered hypothesis-generating.

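### The SAP hypothesises no effect on physical symptoms but plans only tests of difference, with no margin or interval rule, so no planned result can support that hypothesis

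*Combined protocol and SAP*

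**What the plan says.** SAP section 1, Secondary hypotheses, states: "TG-iConquerFear will not affect the prevalence of physical symptoms". The protocol (Study design, RCT) describes the trial type: "This study is a population based randomized controlled clinical superiority trial".

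The planned methods are these:

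- **SAP 5.3, continuous outcomes:** "Continuous secondary outcomes analyzed using paired *t*-tests and between-group comparisons of change scores", plus linear mixed-effects models over time.
- **SAP 5.3, proportions:** "Proportions above/below clinical cut-offs analyzed using" chi-square tests.
- **SAP 5.5:** logistic regression on dichotomised outcomes, with bodily distress given as an example, under the heading of associations with functional disorders.
- **Significance level:** the protocol (Statistical analysis) says "All statistical tests will be two-sided (level of significance = 0.05", and SAP section 8 agrees.
- **SAP section 7:** "No formal adjustments planned. Secondary and exploratory analyses considered hypothesis-generating".

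The SAP's list of secondary outcomes (section 4) includes "Anxiety, depression, and distress (validated scales" but no physical-symptom outcome. The protocol (Secondary outcome measures) does have one, analysed as change from baseline: "Bodily Distress Symptom/somatization, Anxiety and depression* evaluated by relevant Symptom Checklist-90-R (SCL) subscales". The protocol's survey section and timeline also show a BDS checklist, collected at screening and follow-up.

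**The concern.** A hypothesis of no effect needs a rule for deciding when the data are close enough to zero. Such a rule is a margin with an equivalence test, or a stated way of reading a confidence interval. The SAP has neither. A significant difference would contradict the hypothesis, and a non-significant one would agree with it without being evidence for it.

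This matters more in a small trial. As precision falls, non-significance becomes the likely result over a widening range of true effects. A moderate real change in bodily symptoms, in either direction, could then be taken for support of the hypothesis.

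**Working it through.** **Is there a figure of the plan's own to reproduce?** No. No sample size, power or margin is stated for this hypothesis. The revised total of 68 comes without an effect size, so it cannot be reproduced either. With 27 evaluable per arm and 95% power it implies a standardised difference of about (1.960 + 1.645) × √(2/27) = 0.98. A sample sized for an effect that large was not sized to rule out small ones.

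**Inputs from the documents**

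- 1:1 allocation (protocol, RCT).
- 68 participants with 20% dropout (SAP, update of September 2023): 34 per arm; 68 × 0.8 / 2 = 27.2, about 27 per arm.
- 350 participants with 30% dropout (SAP section 2): 350 × 0.7 / 2 = 122.5, about 122 per arm.
- Two-sided 0.05.

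**Assumed, because the documents give no figures:** the prevalence of physical symptoms in each arm, and the size of difference worth noticing. Both are shown as ranges.

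**Step 1. Precision.** The half-width of the 95% CI for a difference in prevalence is 1.96 × √(2p(1−p)/n).

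| n per arm | p = 0.3 | p = 0.5 |
|---|---|---|
| 34 | 0.218 | 0.238 |
| 27 | 0.244 | 0.267 |

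The interval is therefore about ±22 to 24 points at 34 per arm, and ±24 to 27 points at 27.

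**Step 2. Chance of a non-significant result.** This is an exact enumeration of the chi-square test without continuity correction, summing the two binomial distributions over all tables with |z| ≤ 1.96.

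| True prevalences | 34 per arm | 27 per arm |
|---|---|---|
| No difference (30 to 50%) | about 95% | about 95% |
| 30% vs 20% | 83% | 85% |
| 50% vs 30% | 60% | 69% |
| 40% vs 20% | 54% | 62% |
| 30% vs 10% | 43% | 51% |
| 60% vs 30% | 30% | 41% |
| 50% vs 20% | 23% | 34% |
| 40% vs 10% | 14% | 23% |

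A true 10-point difference gives non-significance nearly as often as no difference at all (83 to 85% against about 95%), so that result separates the two cases poorly. At 20 points the outcome depends on the prevalences. At 30 points, power is 0.70 to 0.86 with 34 per arm and 0.59 to 0.77 with 27.

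**Step 3. The same at the initial sample size.** With about 122 per arm, power for 20 points is 0.90 (50% vs 30%), 0.93 (40% vs 20%) and 0.98 (30% vs 10%). A 10-point difference (30% vs 20%) would still be non-significant 56% of the time.

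**Step 4. Would an equivalence test rescue the claim?** Take two one-sided 5% tests, a true difference of zero and 30% prevalence in both arms. An assumed 20-point margin then needs 90 evaluable per arm for 80% power, and a 15-point margin needs 160. With 27 per arm, power at the 20-point margin is 0% by the normal approximation. The interval is wider than the margin allows: the half-width of the 90% CI is 1.645 × √(2 × 0.3 × 0.7 / 27) = 0.205, already more than 20 points.

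**The case against.** The strongest reply is that the SAP never says non-significance will be read as no effect. On this view the line is a clinical expectation, since a psychological programme is not expected to change bodily symptoms, and section 7 makes secondary analyses hypothesis-generating. The first part stands. A reader might infer that the sponsor plans to claim confirmation from a large P value, and no sentence in the documents supports that. But the item is listed as a hypothesis, and no rule is given for judging it. Section 7 deals with multiplicity, which guards against false positives; the risk here is a false reading of no effect.

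Second, the link between this hypothesis and the chi-square test is inferred. The SAP assigns it no outcome, time point or test. The only cut-off among the SAP's secondary outcomes is the FCRI-SF one, and the protocol treats somatization as a change score, although the hypothesis speaks of prevalence. This stands too, and it is a further gap. Mixed models and logistic regression are also planned, and intervals could be drawn from their estimates. But SAP 5.2 promises a 95% CI only under the primary analysis, and 5.3 promises none for proportions.

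Third, the smallness of the trial dates from the 2023 update. This stands for the power figures: at the initial 350, a 20-point difference would be found about 90% of the time or more. It does not supply the missing margin.

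**Conclusion.** The point holds as a mismatch between hypothesis and method. The SAP states a hypothesis of no effect, and nothing in the plan could support it at any sample size without a margin or interval rule. At 68 participants the data would say little either way, with a 95% CI of about ±22 to 27 points. A true 20-point difference would be non-significant 54 to 69% of the time (50% vs 30%, 40% vs 20%), or 43 to 51% for 30% vs 10%.

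A reader might go further and infer that any large change in physical symptoms would probably be missed. The figures do not bear that out, because differences of 30 points would more likely be detected than missed.

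These sizes rest on assumed prevalences, on 68 being the total randomised, and on a chi-square test of a dichotomised measure. The primary outcome and its analysis are not affected.

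**What to change.** In a dated SAP update, restate the item along these lines: *The between-arm difference in physical symptoms (the bodily distress measure already collected, at 3 months) will be estimated with a 95% CI; a non-significant P value will not be taken as evidence of no effect.* Say which instrument is meant, the SCL subscale or the BDS checklist, and give the cut-off if prevalence is kept. Draw no conclusion of no effect. No equivalence margin is needed, and at this sample size one would not help.

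The SAP's deviations note of 10 January 2025 is written in the past tense and refers to participants' outcome data. If data have already been examined, keep the hypothesis in SAP section 1 on record and log this as a change in interpretation, with its date.

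The cost is a sentence or two and no new data. The downside is giving up a claim that the trial could not support.
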